##### Statistical analysis

The statistical significance of ERP components will be tested by comparing their mean amplitudes to zero at ROIs using one-sample t-tests. This method will allow us to focus exclusively on significant responses, and to distinguish significant scalp distributions from noise. Statistically significant ERPs will be considered for further amplitude analysis.

For standard stimuli, levels of naturalness comparisons will be performed by Level × ROI repeated measures ANOVAs on each ERP and group independently. For deviant stimuli, Level × ROI × Deviant repeated measures ANOVAs will be performed.

Group comparisons will be conducted by Group × ROI repeated measures ANOVAs on each ERP and level of naturalness separately, for standard stimuli. Similarly, for deviant stimuli, Group × ROI × Deviant repeated measures ANOVAs will be performed. The effect of reducing the naturalness of voice on emotion processing will be assessed by the comparison between ERPs amplitudes at levels 1–5 for ASD group and ERPs amplitudes calculated in the control group for human voices. We expect to detect less natural voices to help typical processing in ASD children, that is, fewer difference with non-pathological processing of human voices at least natural voices. Based on MMN analysis at maximum peak ROI, the voice leading to the nearest to non-pathological processing in autistic children will be chosen for Stage 3.

Scalp distribution comparisons for standard stimuli will be assessed by Group × Laterality (FP1, F3, F7, T7, C3, P3, P7, O1/AFz, Fz, CPz, Cz, POz, Pz/FP2, F4, F8, T8, C4, P4, P8, O2) repeated measures ANOVAs on each ERP and level of naturalness separately. For deviant stimuli, Group × Laterality × Deviant repeated measures ANOVAs will be conducted.

For all amplitude analysis, normality will be assessed by Shapiro–Wilk test. In case of non-parametric distribution of the data, a transformation will be applied. Mauchly’s test of sphericity will be used to evaluate homogeneity of variances and co-variances. In case of violation of sphericity, a Greenhouse-Geisser correction will be applied in order to test main effects significance. *Post hoc* comparisons will be conducted to assess specific differences (Tukey and Dunnett procedures). In all cases, level of significance will be set at *p* < 0.05 and statistical analysis will be performed with R software.

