##### Statistical analysis on behavioral data

Group comparisons of reaction times will be conducted by a Group × Stimulus (neutral, anger, disgust, fear, happiness, or sadness) repeated measures ANOVAs on each assessment session separately. Time comparisons will be conducted by Assessment Session × Stimulus on each group separately. Normality of reaction times will be assessed by Shapiro–Wilk test. In case of non-parametric distribution of the data, a transformation will be applied. Mauchly’s test of sphericity will be used to evaluate homogeneity of variances and co-variances. In case of violation of sphericity, a Greenhouse-Geisser correction will be applied in order to test main effects significance. Post-hoc comparisons will be conducted to assess specific differences (Tukey procedure).

Group comparisons of number of correct answers will be conducted by one-way ANOVAs for each deviant and assessment session separately. Time comparisons (between assessment sessions) will be tested by one-way ANOVAs on number of correct answers for each deviant and each group separately. Normality and homogeneity of variances will be assessed by Shapiro–Wilk and Bartlett tests, respectively. In case of non-parametric distribution of the data, Kruskal–Wallis test will be applied. *Post hoc* comparisons will be conducted to assess specific differences (Tukey after ANOVA, Wilcoxon tests with *p*-value adjustment by Holm method after Kruskal–Wallis).

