##### Statistical analysis on ERPs data

The statistical significance of ERP components will be tested by comparing their mean amplitudes to zero at ROIs using one-sample *t*-tests. This method will allow us to focus exclusively on significant responses, and to distinguish significant scalp distributions from noise. Statistically significant ERPs will be considered for further amplitude analysis.

Group comparisons will be conducted by Group × ROI repeated measures ANOVAs on each ERP and assessment session separately, for standard stimuli. Similarly, for deviant stimuli, Group × ROI × Deviant repeated measures ANOVAs will be performed.

For standard stimuli, time comparisons will be conducted by Assessment Session × ROI repeated measures ANOVAs on each ERP and group separately. For deviant stimuli, Assessment Session × ROI × Deviant repeated measures ANOVAs will be performed.

Scalp distribution comparisons for standard stimuli will be assessed by Group × Laterality (FP1, F3, F7, T7, C3, P3, P7, O1/AFz, Fz, CPz, Cz, POz, Pz/FP2, F4, F8, T8, C4, P4, P8, O2) repeated measures ANOVAs on each ERP and assessment session separately. For deviant stimuli, Group × Laterality × Deviant repeated measures ANOVAs will be conducted.

For all amplitude analysis, normality will be assessed by Shapiro–Wilk test. In case of non-parametric distribution of the data, a transformation will be applied. Mauchly’s test of sphericity will be used to evaluate homogeneity of variances and co-variances. In case of violation of sphericity, a Greenhouse-Geisser correction will be applied in order to test main effects significance. *Post hoc* comparisons will be conducted to assess specific differences (Tukey procedure).

All statistical analysis will be performed with R software. Level of significance will be set at *p* < 0.05.

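### ERP amplitudes and reaction times have no fixed analysis scale: a Shapiro-Wilk pre-test decides on a transformation, so group effects at different voice levels or sessions can end up on different scales

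*Protocol article*

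**What the plan says.** The same rule appears in three places in the protocol article.

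- **Stage 2, Statistical analysis (ERPs).** "For all amplitude analysis, normality will be assessed by Shapiro–Wilk test", followed by "In case of non-parametric distribution of the data, a transformation will be applied". The error level is general: "In all cases, level of significance will be set at *p* < 0.05". No other level is given for the normality test.
- **Stage 3, Statistical analysis on behavioral data.** Reaction times get the same check and the same consequence. The Group × Stimulus comparisons are "repeated measures ANOVAs on each assessment session separately".
- **Stage 3, Statistical analysis on ERPs data.** The rule is repeated for amplitudes.

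The group comparisons are split. In Stage 2: "Group comparisons will be conducted by Group × ROI repeated measures ANOVAs on each ERP and level of naturalness separately, for standard stimuli". In Stage 3: "Group comparisons will be conducted by Group × ROI repeated measures ANOVAs on each ERP and assessment session separately, for standard stimuli". Deviant stimuli are handled in the same way with a Deviant factor added.

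The level and session comparisons are not split. In Stage 2, "levels of naturalness comparisons will be performed by Level × ROI repeated measures ANOVAs on each ERP and group independently". In Stage 3, Assessment Session is a factor in one ANOVA per group.

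One Stage 2 contrast cuts across levels and groups. The effect of reduced naturalness is judged by the "comparison between ERPs amplitudes at levels 1–5 for ASD group and ERPs amplitudes calculated in the control group for human voices", and the voice nearest to typical processing, on the MMN, goes forward to Stage 3.

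**The concern.** The scale of an outcome determines what a group difference or an interaction means. Here a significance test on the trial data chooses it, and nothing holds the choice constant across analyses whose results will be read side by side.

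Stage 2 asks how far autistic children are from TD children at each voice level. Stage 3 asks whether group differences change from session to session. If one level or session is analysed in raw units and another after transformation, the effects are not in the same unit, and an interaction can appear or vanish through the scale alone.

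An illustration with assumed values: TD children answer neutral pairs in 800 ms and autistic children in 1,200 ms, and both are 20% slower on emotional pairs. In milliseconds the Group × Stimulus interaction is 1,200 × 0.2 − 800 × 0.2 = 80 ms. In logarithms it is log 1.2 − log 1.2 = 0. A session analysed in milliseconds would show an interaction, and a session with identical behaviour analysed in logarithms would not.

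**Working it through.** The article gives no rate at which the normality check is expected to trigger a transformation, so there is no stated figure to reproduce.

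**Inputs from the article**
- Voices: five naturalness levels plus human voice, so k = 6 separate group ANOVAs per ERP.
- Sessions: pre, mid, end and two follow-ups, so k = 5.
- 18 regions of interest (ROIs) are listed under Stage 2, Data Analysis. With five deviants this makes 90 values per child.
- Each Stage 2 child hears three of six blocks. If balanced (assumption), about 20 of 40 children per group, or 40 in total, contribute to each level.
- Stage 3 has 72 children in four groups, and six stimulus types for reaction times.
- Correlation among repeated measures is 0.5 in the sample-size text. A value of 0.8 is added here as a sensitivity check.

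**Step 1: chance of mixed scales.** If each of k analyses is transformed with probability p, independently,

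P(mixed) = 1 − (1 − p)^k − p^k.

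With exactly normal data and one valid test at p = 0.05:
- six voices: 1 − 0.95^6 − 0.05^6 = 1 − 0.7351 − 0.0000 = 26.5%
- five sessions: 1 − 0.95^5 − 0.05^5 = 1 − 0.7738 − 0.0000 = 22.6%

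**Step 2: dependence on what is tested.** The article does not say whether residuals, cells or pooled values are tested. Simulated exactly normal, equally correlated data for 40 children gave these rejection rates. The mixed-scale chance for six voices comes from the Step 1 formula.

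| Unit tested | Rejects, ρ = 0.5 | Mixed | Rejects, ρ = 0.8 | Mixed |
|---|---|---|---|---|
| Residuals or child means (nominal) | about 5% | 26.5% | about 5% | 26.5% |
| Pooled, 18 ROIs | 25.8% | 83% | 78.2% | 77% |
| Pooled, 90 ROI × deviant values | 62.3% | 94% | 99.2% | 5% |
| Any of 36 cells | 82.7% | 68% | 71.0% | 87% |
| Any of 180 cells | 99.8% | 1% | 97.8% | 12% |

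Pooling clustered values inflates the rejection rate, but a test that rejects almost always puts all voices on one scale again. The mixed-scale risk is largest at intermediate rejection rates.

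**Step 3: skewed reaction times.** Lognormal values (assumed), with one value per child, n = 72 and five sessions:

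| Log-SD | Rejects | Mixed over 5 sessions |
|---|---|---|
| 0.2 | 39.4% | 91% |
| 0.3 | 73.5% | 78% |
| 0.4 | 90.8% | 38% |
| 0.5 | 99.1% | 4% |

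If 72 × 6 lognormal values are pooled instead, the test rejects in 98.6% at log-SD 0.2 (mixed 7%) and in 100% at 0.3 and 0.4 (mixed 0%). Pooled normal values reject in 9.5% (mixed 39%).

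**Step 4: which comparisons are exposed**
- *Exposed:* group effects read across separately analysed levels (Stage 2) or sessions (Stage 3), and the contrast of autistic levels 1–5 with the TD human voice if its amplitudes come from the level-wise analyses.
- *Not exposed:* comparisons inside the Level × ROI, Assessment Session × ROI and Assessment Session × Stimulus ANOVAs, with or without Deviant. Each holds all levels or sessions on one scale.

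All mixed-scale figures treat the analyses as independent. The same children recur across sessions, and partly across levels, so positively related pre-tests would lower them.

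**The case against.** The strongest reply is that the article never says the scale is decided afresh in each ANOVA. It states a check for all amplitude analyses, and one decision per outcome would fit those words. The unit tested and the name of the transformation are details that an article may leave to the full plan. The analyses that directly compare levels or sessions share one scale, and a direct contrast of autistic levels 1–5 with the TD human voice would itself need one. Much of this stands. A decision per analysis is an inference, although a natural one, because the group ANOVAs are run separately and no shared scale is set. The point rests on the rule the article does state, not on the omitted details.

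Three stronger readings are tempting and are not supported.

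- *The rule fires mostly by false alarm.* A reader might infer this from the pooled and cell-wise rates in Step 2. Those rates hold only if raw clustered values are pooled or many cells are tested; on residuals or child means the rate is about 5%. With a valid 5% test, false alarms outnumber true detections only if the share of truly normal analyses exceeds power / (power + 0.05): 0.80 at power 0.2, 0.89 at 0.4 and 0.94 at 0.8. For skewed reaction times most rejections would be correct.
- *Levels and sessions necessarily end up on different scales.* It is a possibility whose size depends on unstated conditions, and it can be close to zero.
- *The one-sample tests against zero lose their zero.* Those tests are an earlier screening step. Nothing says they use transformed data, and sign-preserving transformations keep zero.

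**Conclusion.** The concern holds in a limited form. The article lets a Shapiro-Wilk result on the trial data choose the scale for ERP amplitudes and reaction times and fixes no common scale across the separately run group analyses. Even on the reading most favourable to a per-analysis check (exact normality, one valid 5% test per ANOVA, independent analyses), the scales differ somewhere with probability 26.5% across six voices for each ERP and 22.6% across five sessions for each outcome. Pooling of clustered values or moderate skew often raises this, and near-certain rejection lowers it.

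What is affected is the comparability of group effects across levels and sessions, including the autistic-level against TD-human contrast that informs the choice of voice. It is not shown that any particular result would be wrong. This is a cheap improvement to a stated rule, worth making before the data are analysed.

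**What to change.** Replace the transformation sentence in the three sections (Stage 2 Statistical analysis; Stage 3 Statistical analysis on behavioral data; Stage 3 Statistical analysis on ERPs data) with a fixed scale for each outcome, valid for all groups, levels and sessions:

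- ERP amplitudes are analysed in microvolts.
- Reaction times are analysed as logarithms.
- Normality is checked on model residuals or child-level means, and the result does not change the scale.
- If ERP residuals are clearly non-normal, the microvolt analysis is kept and a permutation or bootstrap test with the child as the unit is added as a robustness check.

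The chance that the pre-test produces mixed scales then becomes zero. The cost is three sentences of wording and a little extra analysis, with no additional data. Reaction-time effects will be reported as ratios rather than differences in milliseconds.

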#### Participants

Typically developed participants will be recruited from a public announcement posted on Tecnologico de Monterrey, Campus Monterrey. Autistic participants will be recruited by contacting parents of autistic children attending San Jose Hospital from Tecnologico de Monterrey.

Sample size estimation was calculated with G^∗^Power software version 3.1.9.7 (Faul et al., 2007) for Cohen’s d effect size index of 0.8, correlations among repeated measures of 0.5, statistical significance set at *p* < 0.05. For level comparisons, results indicated that 20 participants in each group would be enough to provide an estimated power of 0.90. For group comparisons, results indicated that 38 participants in each group would be enough to provide an estimated power of 0.91.

Forty high-functioning autistic volunteers aged 9 to 11-year-old will be involved in this stage of the research. All autistic participants will be diagnosed by a clinician according to DSM-V (Diagnostic and Statistical Manual of Mental Disorders, Fifth Edition) (American Psychiatric Association, 2013) or the International Classification of Diseases and Related Health Problems – Tenth Edition (World Health Organization, 1994) criteria. Autistic symptomatology will be assessed by the Autism Spectrum Rating Scales (ASRS) – parent report (Goldstein, 2012). A T-score greater than 60 (slightly elevated to very elevated scores for autistic behaviors) on Social/Communication, DSM-IV-TR (Text Revision), Peer and Adult Socialization and Social/Emotional Reciprocity domains will be considered as an inclusion criterion.

In addition, 40 TD volunteers aged 9 to 11-year-old will be included in this study. Similar to autistic children, ASRS will be used, and children with a score inferior to 60 in all scales will be included.

Any TD or autistic participant will be excluded if child:

•is under medication affecting the central or peripherical nervous system,•has hearing loss or deficits, and/or•has history of a developmental pathology and/or any disease affecting behavior and nervous system, apart from ASD for autistic participants.

### An Intervention Based on Social Stories^TM^, Synthesized Voices and Interactions With NAO

This last stage of the research aims to implement the use of the synthesized voice selected in Stage 2 in a 2-week intervention for autistic children. The intervention will aim to train emotions differentiation skills when triggered by prosody and will implement the Social Story^TM^ method while interacting with a social robot (NAO). Pre- and follow-up intervention assessments will be conducted using the ASRS questionnaire – parents form, completed with EEG and behavioral correlates of emotions differentiation. Considering the 4-week sensitivity of the ASRS questionnaire, mid- and end-intervention assessments will only be conducted by EEG and behavioral data analysis. A substantial improvement in social and emotional skills at end and follow-up assessments is expected.

#### Intervention

The intervention will consist of six-time per week sessions for 2 weeks conducted in a one-to-one format. Each session will last approximatively 10 min and will be composed of two Social Stories^TM^: one general and one specific. General Social Stories^TM^ will describe and compare all emotions. Specific ones will describe only one emotion. At the end of the first week, the child will have been presented with a specific story for each emotion and three different general stories. During the second week, the same stories will be repeated in a different order. Presentation order will be random and different for each participant. The stories will be uttered by NAO social robot that will be previously programmed using Choregraphe software (Femmam, 2017). Emotional and neutral speech will be uttered using the synthesized voiced selected in Stage 2. Each Social Story^TM^ will be written to train emotion differentiation and recognition through prosody (please see section “Social Stories^TM^ Elaboration” for more details and Supplementary File 1 for an example of a Social Story^TM^). Questions about the emotion conveyed will be asked to the participant. Correct responses will lead to a social reinforcement (e.g., “Well done!” ^∗^in Spanish^∗^ saying with a happy prosody and synthesized voice). Incorrect or absence of response will result in repeating the part of the story that contains the information necessary to answer the question. Then the question will be asked again, and a correct answer will lead to a social reinforcement. In case of incorrect answer, the correct answer will be told by the robot. In case of correct answers, the robot will specify that in daily life, this emotion may not be uttered by the synthesized voice but will be better uttered by his entourage with a more natural voice. Then the robot will repeat the same emotional utterance with the human voice and ask which emotion is conveyed. Again, correct responses will lead to social reinforcement. Incorrect or absence of response will result in repeating the part of the story that contains the information necessary to answer the question. Then the question will be asked again, and a correct answer will lead to a social reinforcement. In case of incorrect answer, the correct answer will be told by the robot. Each session will start with robot NAO friendly inviting the participant to play the “emotion game” and explaining the instructions. Robot’s movements and eye lighting will only be programmed for this part. During Social Stories^TM^, NAO will remain still in order to focus the child’s attention to the auditive information. All session long, NAO will be remotely controlled by the researcher with a Wizard-Of-Oz method using the Graphical User Interface provided by the system (Cao et al., 2019).

#### Outcome Measures

##### ASRS questionnaire

The ASRS questionnaire is a standardized, reliable and validated set of questions targeted to parents or teachers of autistic people aged between 2 and 18 years to measure their autistic symptomatology (Simek and Wahlberg, 2011). It presents several advantages for its use in research (Goldstein, 2012). First, a wide range of autistic social and emotional behaviors are assessed, so that it makes the evaluation of generalization of learning to other social domains possible. Second, the scores provided are based on a normative TD sample, thus it considers the autism spectrum as a continuum with the general population making possible the comparison with a TD control group. The full-length version for 6–18 years old children and youths is composed of 71 items divided in three scales: ASRS scale, DSM-IV, and Treatment Scale. A 4-level scale is presented to the rater in order him to specify how often a particular behavior is used to be observed in the child or youth that is evaluated. Higher scores indicate higher symptoms severity according to the rater. In this study, a particular focus will be dedicated to Social/Communication, DSM-IV-TR, Peer and Adult Socialization and Social/Emotional Reciprocity domains. Parents of both groups will answer this questionnaire on pre-intervention (1st session) and follow-up sessions (2 and 6 weeks after the end of the intervention).

##### Behavioral assessments

At pre- (1st session), mid- (7th session), end- (13rd session), and follow-up sessions (2 and 6 weeks after the end of the intervention), participants will be asked to answer the following behavioral task. It will consist of one block of stimulus pairs containing 244 pairs that will be presented at 60 dB via the Shure SRH1840 audio headset. The stimulus pair will be composed of either identical stimuli (50%; two neutral stimuli), or different stimuli [one neutral and one of the emotional deviants (50%; anger (10%), disgust (10%), fear (10%), happiness (10%), or sadness (10%)]. Fifty percent of pairs that contain a deviant stimulus will be composed of 1 neutral followed by 1 emotional stimulus, and 50% will be composed of 1 emotional followed by 1 neutral stimulus. Word pairs will be equally uttered with a male, woman, or child voice. The within-pair stimulus onset asynchrony will be 1,300 ms, and the between-pair stimulus onset asynchrony will be 2,600 ms. The order of stimulus pairs will be randomized between participants, but the stimulus sequence will be fixed. During this approximately 20-min task, participants will have to answer by pressing previously instructed keys on a laptop keyboard, if the emotional prosody of both stimuli of each pair will be the same or different. If they choose different, they will have to mention the emotion conveyed by the deviant (anger, disgust, fear, happiness, or sadness). Reaction times and correct/incorrect answers will be recorded. To make sure that the participant understands the task, three training trials will be presented before the test. Autistic participants will be accompanied by their parent if necessary.

